## Abstract

**Background::**

Vascular cognitive impairment (VCI) has a decline in the ability of learning, memory, understanding and execution, which seriously interferes with the daily life of patients. Type 2 diabetes mellitus (T2DM) is an important risk factor for VCI. In recent years, the pathogenesis and treatment of VCI with T2DM have become a research hotspot. Acupuncture-rehabilitation therapy plays an important role in the treatment of various functional disorders of cerebrovascular diseases. In the previous study of the research group, it has been proved from the perspective of imaging that acupuncture-rehabilitation therapy can improve the cognitive function of patients with ischemic stroke. Based on the previous research results, we speculate that acupuncture-rehabilitation therapy not only improves the function of cognitive-related brain regions, but also affects its structure, as well as serum biomarkers highly related to T2DM and cognitive function.

**Methods/Design::**

A partial randomized controlled trial will be conducted at the Second Affiliated Hospital of Heilongjiang University of Chinese Medicine, between July 1, 2021 and December 31, 2023. A total of 80 subjects will participate in the trial, including 25 healthy volunteers, 25 T2DM patients with normal cognitive function and 30 VCI patients with T2DM. They will all have at least 1 functional magnetic resonance imaging scan. Through the calculation and analysis of voxel-based morphological analysis indexes, the changes of hippocampal volume and function in the 3 groups are compared, so as to confirm the correlation between hippocampal structural and functional changes, between T2DM patients and healthy volunteers, as well as T2DM patients with normal cognitive and VCI patients with T2DM. Then the VCI patients with T2DM were randomly divided into 2 groups. The control group was given routine drug treatment to control blood sugar and improve cognitive function, and the experimental group was treated with acupuncture-rehabilitation therapy on the basis of the control group. Patients in both groups will receive serum biomarkers (superoxide organic dismutase, maleic dialdehyde, brain-derived neurotrophic factor) detection and neuropsychological scale (Montreal Cognitive Assessment, Webster Memory Scale IV Chinese version (adult version), functional independent measurement) evaluation before treatment, 4 weeks, 8 weeks, and 12 weeks after treatment. The functional magnetic resonance imaging scan will be performed again after 12 weeks of treatment. To observe the effect of acupuncture-rehabilitation therapy on cognitive function of VCI patients with T2DM.

**Discussion::**

This trial can clarify the effect of acupuncture-rehabilitation therapy on hippocampal volume and its intervention mechanism on oxidative stress injury in VCI patients with T2DM, and clarify the scientific connotation of its neuroprotective mechanism in the VCI patients with T2DM, in order to provide a theoretical basis for the clinical application of acupuncture-rehabilitation therapy in the treatment of VCI.

**Trial registration::**

Chinese Clinical Trial Registry (ChiCTR), ChiCTR2100047803. Registered 26 June, https://www.chictr.org.cn/showproj.aspx?proj=128707

## Introduction

1

Vascular cognitive impairment (VCI) is a clinical stroke or subclinical vascular brain injury caused by cerebrovascular disease and its risk factors. It involves clinical syndrome with at least one cognitive domain impairment, ranging from mild cognitive impairment to dementia, as well as varying degrees of cognitive impairment caused by mixed pathology such as AD.^[1,2]^ The onset of the disease is hidden, which is mainly manifested by the decline in the ability of learning, memory, understanding and execution, which seriously interferes with the patient's daily life and brings heavy pressure and burden to the patient's family and society. Diabetes mellitus (DM), especially type 2 diabetes mellitus (T2DM) is an independent risk factor for VCI. T2DM can not only cause angiopathy, increase the risk of stroke, but also directly lead to cognitive impairment. Therefore, in recent years, the pathogenesis and treatment of VCI with T2DM have increasingly become a research hotspot.

Cognition is a psychological activity in which individuals know and understand things, including memory, computing power, time-space orientation, executive ability, language understanding, expression and application, among others.^[3]^ Cognitive activities are jointly participated by cerebral cortex, white matter, limbic system, interstitial nuclei, brainstem nuclei, and cerebellum. Different cognitive activities activate different brain regions and subcortical structures. Among them, the hippocampus is most closely related to learning, memory, cognition, and emotion. The left hippocampus plays a dominant role in learning and episodic memory, whereas the right hippocampus is mainly related to non-verbal memory. Therefore, bilateral hippocampus injury will cause severe memory loss. The hippocampus is extremely sensitive to changes in blood glucose and blood oxygen levels. Persistent hyperglycemia and hypoxia will damage the structure and function of the hippocampus and cause abnormal emotional and cognitive behavior and other clinical symptoms.

Diabetes is a group of metabolic diseases characterized by chronic hyperglycemia caused by multiple causes. The mainly clinical manifestations are polydipsia, polyphagia, polyuria, and weight loss. The main pathological manifestations are impaired blood glucose control and insulin resistance.^[4]^ Many studies have shown that T2DM is one of the causes of brain injury, and contributes to vascular cognitive dysfunction particularly. In the study of “Effect of acupuncture-rehabilitation therapy on BOLD-functional magnetic resonance imaging (fMRI) and serum biomarkers in cognitive dysfunction after ischemic stroke patients,” it was found that 19 of 30 nondementia subjects with cognitive impairment after ischemic stroke were complicated with T2DM. It has been proved from the perspective of imaging that acupuncture-rehabilitation therapy can improve the Reho and ALFF values in some brain regions of patients with cognitive impairment after ischemic stroke, strengthen spontaneous functional activities, improve cognitive function.

Based on the above research results, we propose the following scientific questions:

First, acupuncture-rehabilitation therapy can improve the learning and memory function of VCI patients with T2DM, and have a beneficial effect on the volume of hippocampus and the structure of neurons, thus improving cognitive function.

Second, acupuncture-rehabilitation therapy can improve the activity of superoxide orgotein dismutase (SOD) and downregulate the content of malefic dialdehyde (MDA) in peripheral blood of VCI patients with T2DM, and upregulate the expression of brain-derived neurotrophic factor (BDNF), so as to play the role of anti-oxidative stress and brain protection.

Therefore, this study intends to take voxel-based morphological analysis (VBM) as the main analysis method and SOD, MDA, BDNF as the main observation indexes to explore the curative effect of acupuncture-rehabilitation therapy in VCI patients with T2DM from the point of view of imaging and serology.

## Methods/design

2

### Objectives

2.1

Taking VBM as the main analysis method and SOD, MDA, BDNF as the main observation indexes, the effects of acupuncture-rehabilitation therapy on hippocampal volume and function of VCI patients with T2DM and its intervention mechanism on oxidative stress injury in peripheral serum were discussed from the perspective of imaging, and the scientific connotation of its neuroprotective mechanism on patients with VCI complicated with T2DM was clarified.

### Trial design

2.2

This is an outcome assessor- and data analyst-blinded, partial randomized controlled trial conducted at the Second Affiliated Hospital of Heilongjiang University of Chinese Medicine from January 1, 2021 to December 31, 2023. A total of 80 subjects who met the inclusion criteria including 25 healthy volunteers, 25 T2DM patients with normal cognitive function, and 30 patients with VCI combined with T2DM were recruited into the study. First, they were scanned by fMRI, through the calculation and analysis of VBM indexes, the changes in hippocampal volume and function in the 3 groups of patients were compared to determine the difference between type 2 diabetes patients and healthy volunteers, correlation between hippocampal structural and functional changes in patients with normal cognitive T2DM and VCI patients with T2DM. Then, 30 VCI patients with T2DM were randomly divided into the experimental group and the control group, the control group was given routine drug therapy to control blood glucose and improve cognitive function, the experimental group was given acupuncture-rehabilitation therapy on the basis of the control group. The primary outcomes were obtained by VBM calculation and serum biomarkers (SOD, MDA, BDNF) detection, and the secondary outcome indexes were assessed by neuropsychological scales such as Montreal Cognitive Assessment (MoCA), Wechsler Memory Scale IV edition (WMS-IV), FIM, among others. Serum biological indicators and neuropsychological scale will be conducted before treatment, as well as 4 weeks, 8 weeks, and 12 weeks after treatment respectively, fMRI scan will be conducted before treatment and 12 weeks after treatment respectively, to observe the intervention effect of acupuncture-rehabilitation therapy on cognitive function of VCI patients with T2DM. Figure 1 and Table 1*present the technology roadmap and clinical observation flow charts, respectively.*

**Figure 1 F1:**
[figure not shown]
Present the technology roadmap.

**Table 1 T1:** Timing of treatment assessments and data collection.

Research stage	Selection period	Baseline period	Treatment period		
Evaluation times	First time		Second time	Third time	Fourth time
Evaluation times point	1 or 0 day before treatment		4 wk after intervention ± 3 days	8 wk after intervention ± 3 days	12 wk after intervention ± 3 days
Inclusion criteria	×				
Exclusion criteria	×				
Informed onsent form		×			
Random grouping		×			
General assessment					
General information		×			
Present medical history/allergic history		×			
History/complications		×			
Physical check		×	×	×	×
CDR		×			
MMSE		×			
IADL		×			
Evaluation of the curative effect index					
Laboratory examination		×	×	×	×
fMRI scan		×			×
MoCA		×	×	×	×
WMS-IV		×	×	×	×
FIM		×	×	×	×
Security assessment					
Life indication		×	×	×	×
Other assessments					
Drug combination		×	×	×	×
Adverse reactions/events			×	×	×
Treatment compliance			×	×	×

CDR = clinical dementia scale, IADL = instrumental activity of Daily living scale, fMRI = functional magnetic resonance imaging, MMSE = Mini Mental State scale, MoCA = Montreal Cognitive Assessment, WMS-IV = Wechsler Memory Scale IV edition

### Ethics

2.3

This trial was approved by the ethics committee of the Second Affiliated Hospital of Heilongjiang University of Chinese Medicine on 4 April, 2020 (reference number: 2020-K21). All participants will sign an informed consent form, and their real name will not appear in related reports to protect their privacy.

### Study setting

2.4

All participants in this trial will be recruited from the Second Affiliated Hospital of Heilongjiang University of Chinese Medicine. Interventions for all participants will be carried out in the hospitals where the participants are recruited. The Second Affiliated Hospital of Heilongjiang University of Chinese Medicine will be responsible for this trial coordination and data management.

### Sample size

2.5

We will conduct this study using a partial randomized controlled trial design, and the main observed outcome will be improvements in VCI patients with T2DM cognitive function. Our previous clinical observation found that 4 weeks of acupuncture-rehabilitation therapy treatment and routine drug therapy can improve scores on the MoCA scale by 3.13 ± 0.75 and 1.53 ± 0.33 points, respectively.^[5]^ Use PASS15.0 software to calculate, with the significance test level set at 0.05 and the test power at 0.9, the required sample size was 13 subjects for each group. Considering a dropout rate of 15%, a total of 30 subjects needed to be enrolled in VCI group with T2DM (15 participants per group). Then the Healthy volunteers group and T2DM group with normal cognitive function group were matched with the corresponding patient volume (25 participants per group). Therefore, a total of 80 subjects were included in this study.

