### Outcome measures

2.21

All participants will be were evaluated for serum biological indicators and neuropsychological scales before treatment, 4 weeks of treatment, 8 weeks of treatment, and 12 weeks after treatment. fMRI scans were performed before treatment and 12 weeks after treatment. All treatment evaluations will be conducted by researchers who will be blinded to the treatment allocation.

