#### Statistical processing and result presentation of brain function data

2.29.2

Statistical analysis is carried out by using DPASFA, SPM12, Xjview, Rest, and other software based on MATLAB platform.

The values of VBM, ReHo, and FC of healthy volunteers, T2DM cognitive normal group, and VCI group with T2DM were analyzed by ANOVA, with sex, age and years of education as covariates. The test level was set to: cluster level *P* < .05 (FWE or FDR correction). If *P* < .05 and could at least pass the FDR correction, there was a significant difference between the 2 groups of patients and healthy volunteers, which was statistically significant.

In the VCI group with T2DM, the data of VBM, ReHo, and FC in the experimental group and the control group were compared by double-sample *t* test. Paired-sample *t* test was used for intra-group comparison between the 2 groups before and after treatment. The test level was set as: cluster level *P* < .05 (FWE or FDR correction). If *P* < .05 and could at least pass the FDR correction, it was considered that there was a significant difference between the experimental group and the control group, which was statistically significant.

The statistical results were presented by Xjview and Mricron software.

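### The sample size is built on 4-week MoCA, a secondary outcome; the declared primaries (VBM, SOD, MDA, BDNF) have no stated power, and nothing controls error across them

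*Protocol article*

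**What the plan says.** Section 2.5 (Sample size) states that "the main observed outcome will be improvements in VCI patients with T2DM cognitive function". Its planning effect comes from the group's own earlier observation that "4 weeks of acupuncture-rehabilitation therapy treatment and routine drug therapy" "can improve scores on the MoCA scale by 3.13 ± 0.75 and 1.53 ± 0.33 points, respectively". Then, "with the significance test level set at 0.05 and the test power at 0.9", it reports that "the required sample size was 13 subjects for each group", raised to 15 per group for 15% dropout.

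Section 2.2 (Trial design) ranks the outcomes differently: "The primary outcomes were obtained by VBM calculation and serum biomarkers (SOD, MDA, BDNF) detection", with MoCA, WMS-IV and FIM secondary. Sections 2.23 and 2.24 repeat that ranking, and section 2.1 (Objectives) is about hippocampal volume and function and oxidative stress.

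Section 2.21 (Outcome measures) schedules "serum biological indicators and neuropsychological scales before treatment, 4 weeks of treatment, 8 weeks of treatment, and 12 weeks after treatment". MRI is done only before treatment and at week 12 (2.2, 2.21, Table 1).

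Section 2.29.1 compares the two groups on blood markers and scales by t test and treats P below .05 as significant. Section 2.29.2 tests imaging at cluster level 0.05 with FWE or FDR correction and accepts a result that "could at least pass the FDR correction".

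**The concern.** The protocol gives two incompatible answers to the question of which outcome decides the trial. By 2.5 it is cognition, sized on MoCA at week 4 of a 12-week treatment. By 2.2, 2.23 and 2.24 it is one imaging measure and three serum markers. A later analysis plan cannot make both statements true.

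Two things follow. A reader who sees power 0.9 will take it to cover the primary outcomes, and it does not. And because no primary leads and no primary visit is named, one nominally significant result for SOD, MDA or BDNF, at any of three visits, or one VBM cluster, could be reported as a positive primary result. A MoCA result could also be presented as the main outcome on the strength of 2.5.

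**Working it through.** **1. The plan's own figure.** Inputs from 2.5: mean changes 3.13 and 1.53, SDs 0.75 and 0.33, alpha 0.05 (taken as two-sided, since sidedness is not stated), power 0.90.

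- Difference = 3.13 − 1.53 = 1.60.
- Pooled SD = √[(0.75² + 0.33²)/2] = 0.579, so d = 1.60/0.579 = 2.76.
- Normal approximation, n = 2[(1.960 + 1.282) × SD/difference]²: 2.76, so 3 per group, with the pooled SD; 4.62, so 5 per group, with SD 0.75 in both arms.
- Exact (noncentral) t: 5 per group with the pooled SD, 6 with SD 0.75.
- Power at 13 per group: above 99.9% with either SD.

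The stated 13 is not reproduced. For a 1.60-point difference, 13 per group at 90% power would need an SD of about 1.21 (exact t), which the protocol does not give.

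**2. What 13 completers per group can detect.** 15 × 0.85 = 12.75, so about 13 completers. The protocol gives no effect or SD for any declared primary, so only standardised differences can be shown (two-sided, noncentral t). The true effects in the last four columns are assumptions.

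| Alpha | d for 90% power | Power, d = 0.5 | d = 0.8 | d = 1.0 | d = 1.2 |
|---|---|---|---|---|---|
| 0.05 (single primary) | 1.33 | 23% | 50% | 69% | 84% |
| 0.0125 (= 0.05/4) | 1.59 | 10% | 28% | 46% | 64% |

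**3. Chance of at least one false positive.** VBM is treated as one test at 5%, because its correction acts within the map. Under independence the formula is 1 − 0.95^k.

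- Three serum markers at one visit: 1 − 0.95³ = 14.3%.
- Four primaries at week 12: 1 − 0.95⁴ = 18.5%.
- Three markers at three visits, plus VBM: 1 − 0.95¹⁰ = 40.1%.

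Repeated measurements on the same patients are correlated, which lowers the last figure. The protocol gives no correlations, so these are assumed. With correlation 0.8 between visits, simulation at 13 per group gives about 24% for the nine serum tests if the markers correlate at 0.5, and about 27% if they are uncorrelated. Adding VBM as an independent test gives 1 − 0.76 × 0.95 = 28% and 1 − 0.73 × 0.95 = 31% from these rounded values (30% unrounded).

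**The case against.** Several stronger readings are tempting, and the document does not support them.

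- *All four primaries are tested unadjusted at several visits.* This is true of the serum markers only. VBM has a single post-treatment scan and a cluster-level correction. Accepting either FWE or FDR is loose, but it is not an absence of correction.
- *The primaries are unpowered.* The document shows only that no power is stated. Without an effect and SD, the true power is unknown.
- *VBM will be run over the whole brain although the aim is hippocampal.* Section 2.29.2 names no search volume, and 2.2 speaks of hippocampal changes. The whole-brain wording in the Discussion describes the technique in general.
- *There will be ten primary tests.* Section 2.29.1 does not say that each visit is a separate primary claim. Ten is what the stated rule permits.

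It can also be said that the primary time point and multiplicity rules usually belong in the statistical analysis plan, which 2.28 assigns to a third party. That is fair, and silence on them alone would be no finding. But the conflict between 2.5 and 2.2, 2.23 and 2.24 is in the protocol itself, and 2.29.1 already fixes a 0.05 decision rule for the serum markers.

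**Conclusion.** The point holds in this limited form. The sample size rests on a declared secondary outcome at week 4, so the stated power of 0.9 covers no declared primary. It is also not the right figure for MoCA, where the quoted inputs give more than 99.9% power at 13 per group. No effect, SD or power is stated for VBM, SOD, MDA or BDNF. The serum markers carry an unadjusted 0.05 rule, and the imaging correction does not reach across the four primaries.

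The false-positive risk is 18.5% for four independent tests at week 12. It is at most about 40% if every visit counts, and about 28 to 30% under the assumed correlations. The detectable effect of 1.33 SD assumes 13 completers per group, one primary and two-sided 0.05. The contradiction should be settled before analysis, because as written the main outcome can be chosen after the results are seen.

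**What to change.** 1. Reconcile 2.5 with 2.2, 2.23 and 2.24 by naming one primary outcome at week 12. Hippocampal grey-matter volume fits objective 2.1. If cognition is the real question, make it MoCA; the protocol has no week-12 planning effect for MoCA, so one must then be sourced.
2. Test the remaining primary-level outcomes at week 12 only after the first succeeds, by Holm or in a fixed order. Label weeks 4 and 8 supportive.
3. In 2.29.2, choose FWE or FDR in advance.
4. In 2.5, state that the calculation was made for 4-week MoCA and not for the declared primaries. Correct or re-source the 13 per group. Add that 13 completers per group give 90% power for about 1.33 SD at two-sided 0.05 for a single primary.

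The cost is a change of wording in the protocol, carried into the analysis plan. Individual biomarkers face a stricter threshold, and the stated sensitivity looks less favourable. No extra patients, scans or blood samples are needed, provided the sponsor accepts that only large effects can be detected reliably at this size.

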### Secondary outcome measures

2.24

**MoCA Scale:** The MoCA is presently recognized as one of the cognitive impairment screening scales, which mainly includes attention, executive function, memory, speech, visual space structure, abstract thinking, calculation ability, and other aspects of screening.^[8]^ Compared with the MMSE, MoCA has better sensitivity and specificity for mild cognitive impairment. The total score of MoCA is 30 points. If the subject has been in education for ≤12 years, 1 point is added. A score <26 points is considered to have cognitive impairment.

**WMS-IV:** The Wechsler Memory Scale (WMS) is a set of tests to assess various memory abilities and working memory. It can provide detailed evaluation of clinical memory function for patients suspected of having memory deficits, psychiatric diseases, or developmental disabilities. The WMS was released in 1945 and has been revised to the fourth edition(WMS-Fourth edition) in 2008,^[9]^ WMS-IV has adjusted and improved the structure and content of the original scale, extended the age of the subjects to 16 to 90 years’ old, and added 4 subscales (concise cognitive status assessment, graphic recognition, spatial superposition, symbol breadth), and provide auditory memory, visual memory, visual working memory, instant memory and delayed memory, and total memory quotient to explain the individual's memory ability.^[10]^ Not only to assess memory function, but also to make a brief assessment of cognitive function status.

**FIM:** The FIM is a comprehensive and objective assessment method that reflects the patient's activities of daily living. It selects the most common and useful 18 functional assessment items (including 6 self-care activities, 2 sphincter control, 3 transfers, 2 walking, Communicate 2 items and 3 social cognition items), and determine the appropriate grading scoring method (each item is divided into 7 levels, the highest score is 7 points, the lowest score is 1 point, the total score is the highest 126 points, the lowest 18 points. The higher the score, the better the level of independence, the worse on the contrary.). This scale can comprehensively reflect the patient's function and independent living ability, evaluate and compare the severity of the patient's disability, predict the rehabilitation consequences, formulate rehabilitation goals, select treatment plans, and evaluate the rehabilitation efficacy.

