#### Statistical analysis of general data, behavioral tests, and blood biomarkers

2.29.1

The metrological data of the measured data were expressed as “mean ± standard deviation,” and the normality test was carried out. If all data were in line with normal distribution (*P* > .05), *χ*^2^ test was used for counting data, *t* test was used for measurement data, double-sample *t* test was used for comparison between the 2 groups, and paired-sample *t* test was used for comparison within the group. The test level was *P* = .05, if *P* < .05 indicated statistically significant difference. The above statistical work is analyzed and processed by specialized statisticians using SPSS25.0 statistical software (SPSS Inc, Chicago, IL).

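### The control-arm MoCA spread of ±0.33 cannot be an SD of whole-point changes, and 13 per group does not follow from the printed values, so the stated 90% power is unsupported

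*Protocol article*

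**What the plan says.** Section 2.5 (Sample size) takes its inputs from the group's earlier work, measured at 4 weeks. There the experimental and the control treatment, in that order, "can improve scores on the MoCA scale by 3.13 ± 0.75 and 1.53 ± 0.33 points, respectively". The ± is not labelled as a standard deviation or a standard error, and the earlier study's arm sizes are not given. PASS 15.0 is then run "with the significance test level set at 0.05 and the test power at 0.9", with the result that "the required sample size was 13 subjects for each group". Allowing for dropout: "Considering a dropout rate of 15%, a total of 30 subjects needed to be enrolled in VCI group with T2DM (15 participants per group"). The SD entered, the test and the sidedness are not stated.

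Two other places bear on how the figures are read. Section 2.24 describes the scale: "The total score of MoCA is 30 points. If the subject has been in education for ≤12 years, 1 point is added". Section 2.29.1 says that this trial's own measurements "were expressed as “mean ± standard deviation" and that "double-sample *t* test was used for comparison between the 2 groups".

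**The concern.** The two ± values are the only figures for the variability of a MoCA change in the document, and they stand directly before the power statement. A reader who knows the trial's own mean-and-SD convention will take them as the SDs behind the calculation. Two things then fail. One of the values is impossible as an SD for a score that moves in whole points. And the printed values do not lead to the printed sample size.

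The matter is more than a missing label, because this is the only power statement in the article. If the spread of individual changes is well above 1.2 points, 13 completers per group would have much less than 90% power. A null MoCA comparison could then be misread as evidence of no effect, on the strength of a power figure that nothing printed supports.

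**Working it through.** **Inputs.** From section 2.5: mean improvements 3.13 and 1.53, so a difference of 3.13 − 1.53 = 1.60; ± values 0.75 and 0.33; alpha 0.05; power 0.90; 13 per group, 15 after dropout. From section 2.29.1: two-sample t test. Two-sided testing is assumed below unless stated.

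**1. Trying to reproduce 13.** Taking the ± values as SDs, the pooled SD is √((0.75² + 0.33²)/2) = √(0.6714/2) = 0.579.
- Normal approximation: n = 2 × (1.960 + 1.282)² × 0.579² / 1.60² ≈ 2.8, so 3 per group.
- Noncentral t: 5 per group two-sided, 4 one-sided.
- SD 0.75 in both arms: 5 to 6 per group two-sided.
- Power at 13 per group with 0.75 and 0.33: above 99.9%.

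No reading of the two values as the arms' SDs gives 13.

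**2. Which SD does give 13?** Solving backwards for a common SD with a difference of 1.60 and 90% power, 13 per group corresponds to about 1.16 to 1.21 by the t test, or 1.21 to 1.26 by the normal approximation. One-sided t testing would need about 1.30 to 1.35. None of these appears in the document. Power at 13 per group by common SD (t test):

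| Common SD | Power |
|---|---|
| 1.0 | 97% |
| 1.2 | 90% |
| 1.5 | 74% |
| 2.0 | 50% |

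**3. Is 0.33 possible as an SD?** Section 2.24 gives a 30-point total and a correction of one whole point, and the eligibility cutoffs in sections 2.9.1 to 2.11 are whole points. The correction cancels within a patient, and each change is a whole number. A whole-number variable whose mean has fractional part f has its smallest SD when every value is one of the two neighbouring integers, and that SD is √(f(1 − f)).
- Mean 1.53: √(0.53 × 0.47) = 0.499. Over the rounding interval 1.525 to 1.535 the floor is 0.4994 to 0.4988, so rounding does not rescue 0.33. The usual n − 1 divisor only raises the floor.
- Mean 3.13: √(0.13 × 0.87) = 0.336, so 0.75 is admissible.

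The control-arm value fails; the experimental-arm value does not.

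**4. Does the impossibility itself lower power?** No. Replacing 0.33 by its floor of 0.50, with 0.75 in the other arm, gives 4 to 5 per group and still more than 99.9% power at 13.

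**5. Scenario: the ± values are standard errors (an assumption).** Then SD = SE × √n₀, where n₀ is the source arm size. For n₀ = 15: 0.75 × √15 = 2.90, 0.33 × √15 = 1.28, pooled √((2.905² + 1.278²)/2) = 2.24. Equal-variance t test, difference 1.60:

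| Assumed n₀ | Pooled SD | Power, 13 per group | Power, 15 per group | n per group for 90% |
|---|---|---|---|---|
| 10 | 1.83 | 57% | 64% | 29 |
| 15 | 2.24 | 42% | 47% | 43 |
| 20 | 2.59 | 33% | 37% | 57 |
| 30 | 3.17 | 23% | 27% | 84 |

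The means would fit arms of 15 (47/15 = 3.13 and 23/15 = 1.53), but arms of 30, 32, 38 and 40 fit as well, so this does not fix n₀.

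**The case against.** The best defence is that section 2.5 never says 0.33 was entered in PASS, nor that the ± is an SD; the mean-and-SD convention in section 2.29.1 covers this trial's data, not the cited earlier study. Since 13 does not come out of 0.75 and 0.33, some other SD may have been used. A run with an SD of about 1.2 would return exactly 13 at 90% power, in which case the design is sound and only the printed ± is unclear or mistyped. This stands as a possibility that the document neither confirms nor excludes. It does not make the paragraph right, because the figures printed as the basis are not the basis.

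A reader might go further and infer that the 90% rests on 0.33 and that the real power is near 40%. The document does not support that. The impossible value alone leaves power above 99.9% when moved to its floor. The figure near 40% needs two undocumented assumptions: that both ± values are standard errors, and that the source arms held about 15 patients. The values could also come from arithmetic on pre- and post-treatment SDs, and then the standard-error figures would not apply.

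It is also fair to say that MoCA is listed as a secondary outcome (sections 2.2 and 2.24). But section 2.5 names cognitive improvement as the main outcome for sizing the trial and uses MoCA for it, so the calculation should hold together.

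**Conclusion.** The point holds in a limited form. As an SD of individual whole-point changes, 0.33 is impossible against a floor of 0.50. This rests only on whole-point scoring, which follows from the article's description of the scale and its cutoffs. Separately, 13 per group at 90% power does not follow from the printed values, which give about 5 per group if read as SDs; it requires a common SD of about 1.2 that is not printed.

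The stated power is therefore unsupported, and its true value cannot be determined from the document. It may be 90% if an SD near 1.2 was used and is correct. It may be about 57%, 42%, 33% or 23% if the ± values are standard errors from arms of 10, 15, 20 or 30. None of these should be reported as the trial's power without the source data.

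**What to change.** In section 2.5, replace the two ± values with the SDs of the individual 4-week MoCA changes, computed from the group's earlier data. Label them as SDs, give the source arm sizes, and check that each is possible for whole-point scores (at least 0.50 for a mean of 1.53 and at least 0.34 for a mean of 3.13). State the SD, the test and the sidedness entered in PASS. Then restate the power that 13 completers per group (15 randomised) give with those SDs, keeping the sample size as it is.

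The cost is a second look at data the group already holds and a few revised sentences, with no added patients or procedures. The downside is that the restated power may be less favourable than 90%.

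### Section 2.5: the stated 13 per group at 90% power does not follow from the MoCA figures printed beside it, which give about 5 per group

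*Protocol article*

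**What the plan says.** Section 2.5 (Sample size) takes its planning values from the group's own earlier work: the combined therapy and routine drug therapy, each given for 4 weeks, were found to "improve scores on the MoCA scale by 3.13 ± 0.75 and 1.53 ± 0.33 points, respectively". It names PASS 15.0 as the software and continues: "with the significance test level set at 0.05 and the test power at 0.9, the required sample size was 13 subjects for each group". The enrolment target follows: "Considering a dropout rate of 15%, a total of 30 subjects needed to be enrolled in VCI group with T2DM (15 participants per group").

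Section 2.5 names no test, does not say whether the 0.05 level is one- or two-sided, and does not label the ± values. The test can be taken from section 2.29.1, which says that for the scales and biomarkers a "double-sample *t* test was used for comparison between the 2 groups".

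**The concern.** The paragraph prints both the inputs and the answer of a standard two-mean calculation, so a reader can check one against the other, and they disagree. This is not detail left to a fuller protocol or an analysis plan. A gap of 1.60 points against SDs of 0.75 and 0.33 is a very large standardised effect, and such effects need only a handful of patients per arm, not 13.

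This is the article's only power statement and it fixes the 30 randomised patients. If it cannot be reproduced, readers cannot tell which variability or settings lie behind the size of the randomised comparison. A smaller question is whether 15 per group delivers 13 completers at the stated dropout rate.

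**Working it through.** **Inputs**
- Mean MoCA gains 3.13 and 1.53, ± values 0.75 and 0.33, significance level 0.05, power 0.9, 13 per group, 15% dropout, 15 enrolled per group: all from section 2.5.
- Two-sample t test: section 2.29.1.
- Assumed, because not stated: ± is an SD, and the test is two-sided.

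**Step 1: standardised effect**
- Difference: 3.13 − 1.53 = 1.60.
- Pooled SD: √[(0.75² + 0.33²)/2] = √[(0.5625 + 0.1089)/2] = √0.3357 = 0.579.
- Effect: 1.60/0.579 = 2.76.

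**Step 2: attempt to reproduce 13**

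Power of the equal-variance t test uses the noncentral t distribution with 2n − 2 degrees of freedom and noncentrality 2.76 × √(n/2):

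| n per group | Power |
|---|---|
| 3 | 71.7% |
| 4 | 89.9% |
| 5 | 96.7% |
| 6 | 99.0% |
| 13 | above 99.99% |

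The smallest n reaching 90% is 5. The stated 13 is 13/5 = 2.6 times that.

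**Step 3: other readings of the same inputs**

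| Reading | n per group |
|---|---|
| Normal approximation: 2 × (1.960 + 1.282)²/2.76² = 2.76, rounded up | 3 |
| One-sided t test (86.7% at 3, 96.2% at 4) | 4 |
| Welch unequal-variance t test (94.2% at 5) | 5 |
| Larger SD, 0.75, in both arms (83.9% at 5, 91.4% at 6) | 6 |
| Variance sum not halved, SD √0.6714 = 0.819 (91.7% at 7) | 7 |
| The two SDs added, 1.08 (91.0% at 11) | 11 |

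The first four are reasonable variants and span 3 to 6. The last two are mistakes someone might make, and even they stop short of 13.

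**Step 4: what 13 per group would correspond to**

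Solving the t-test power for 90% at n = 13 gives a detectable effect of 1.326 SD. With a difference of 1.60 that implies a common SD of 1.60/1.326 = 1.207. With SD 0.579 it implies a difference of 1.326 × 0.579 = 0.77. Neither value is in the article.

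**Step 5: dropout, taking 13 completers as given**
- Required enrolment: 13/(1 − 0.15) = 15.3, so 16 per group.
- The stated 15 matches 13 × 1.15 = 14.95, which adds 15% instead of dividing by 0.85.
- Expected completers from 15: 15 × 0.85 = 12.75.
- Loss that 15 can absorb while keeping 13: 2/15 = 13.3%.
- At an effect of 1.326 SD, 12 completers per group give 87% power against the intended 90%.

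**The case against.** The strongest reply is that the error runs in the safe direction. On the printed inputs the trial enrols three times what MoCA needs (15 against 5), so that comparison is not underpowered. That stands, and it limits the seriousness of the point; it does not make the sentence correct, because 90% power and 13 per group cannot both follow from these inputs.

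A second reply is that sidedness and the meaning of ± had to be assumed, so 5 is one reading. That is fair, and it is why the range of 3 to 6 is given. No reasonable SD-based variant reaches 13.

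Third, the dropout remark is slight and does not add to the main point. It counts as a shortfall only if 13 is accepted as the requirement. If 5 is the requirement, 15 per group covers 15% loss easily. Even against 13 the expected gap is a quarter of a patient per group. This objection stands, and dropout is kept only as a note.

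A reader might also infer that 13 is far too few, by taking ± as a standard error. With assumed earlier-study arms of 10, 15 or 30 patients, that reading would need 29, 43 or 84 per group; with arms of 4 it would give 13. The article states no arm size and does not call the values standard errors, so it does not support that conclusion. It supports only a request to label them.

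**Conclusion.** Wrong as written, and should be fixed. Thirteen per group at 90% power does not follow from the MoCA inputs in section 2.5: they give 5 per group by two-sided two-sample t test (3 to 6 across reasonable variants), and 13 per group would have power above 99.99%. This rests on reading ± as SD; a one-sided test does not change the conclusion.

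Two stronger readings are not supported. One is that the trial is underpowered for MoCA: on the printed inputs it is not. The other is that the targeted effect is unknown: both mean gains are printed, so the 1.60-point difference is explicit, and what is unclear is the variability or other setting used in the software.

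The dropout figure is a minor inaccuracy of one patient per group relative to the stated 13, and would not justify a finding by itself.

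**What to change.** Rewrite the paragraph in section 2.5:
- Report the difference, SD, test and sidedness actually entered in PASS, and say whether the ± values are SDs or standard errors.
- Restate either the required number per group or the power so that it agrees with those inputs.
- If 13 completers per group is kept, say that it detects about 1.33 SD at 90% power. Do not print an SD of 1.21 as a planning assumption unless it was the value used; here it is only solved backwards from 13.
- Describe the dropout cover of 15 per group as about 13% (2 of 15).

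The cost is one reworded paragraph and a slightly less favourable dropout statement. Enrolment can stay at 30, with no extra patients.
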